## Abstract

**Background:**

Obstructive sleep apnea (OSA) is associated with increased risk for cardiovascular morbidity and mortality. Epidemiological and animal models studies generate hypotheses for innovative strategies in OSA management by interfering intermediates mechanisms associated with cardiovascular complications. We have thus initiated the Epigenetics modification in Obstructive Sleep Apnea (EPIOSA) study (ClinicalTrials.gov identifier: NCT02131610).

**Methods/design:**

EPIOSA is a prospective cohort study aiming to recruit 350 participants of caucasian ethnicity and free of other chronic or inflammatory diseases: 300 patients with prevalent OSA and 50 non-OSA subjects. All of them will be follow-up for at least 5 years. Recruitment and study visits are performed in single University-based sleep clinic using standard operating procedures. At baseline and at each one year follow-up examination, patients are subjected to a core phenotyping protocol. This includes a standardized questionnaire and physical examination to determine incident comorbidities and health resources utilization, with a primary focus on cardiovascular events. Confirmatory outcomes information is requested from patient records and the regional Department of Health Services. Every year, OSA status will be assessed by full sleep study and blood samples will be obtained for immediate standard biochemistry, hematology, inflammatory cytokines and cytometry analysis. For biobanking, aliquots of serum, plasma, urine, mRNA and DNA are also obtained. Bilateral carotid echography will be performed to assess subclinical atherosclerosis and atherosclerosis progression. OSA patients are treated according with national guidelines.

**Discussion:**

EPIOSA will enable the prospective evaluation of inflammatory and epigenetics mechanism involved in cardiovascular complication of treated and non-treated patients with OSA compared with non OSA subjects.

## Background

Obstructive sleep apnea (OSA) is the most common respiratory sleep disorder characterized by recurrent episodes of partial or complete pharyngeal obstruction [1]. Though obesity is the main risk to develop OSA, craniofacial morphology and ventilator drive abnormalities are also important in OSA pathogenesis. Collapse of the upper airway during sleep leads to recurrent arousals, intermittent hypoxia, and surges in sympathetic activity. These intermediate mechanics may explain to some extent, the increased risk of mortality [2], incident hypertension [3,4], coronary artery disease [5] and stroke [6] described in OSA. In this context, circulating biomarkers of inflammation and oxidative stress have been described to be elevated in some OSA patients, and lowered with CPAP therapy regardless of weight changes [7]. A cause-effect relationship has been suggested between this systemic inflammatory state and cardiovascular disease, based on the induction of inflammatory processes in the vessel wall [8]. Such processes are considered to be critical determinants of pathological alterations of the vasculature such as thickening of vessel wall, fatty streak formation, or promotion of atherosclerotic plaques. Furthermore, raised levels of proinflammatory cytokines involved in the atherosclerotic process, such as Interleukin-6 (IL-6) and C-reactive protein (CRP), have been reported in OSA. Nevertheless, these cytokines are also increased in obesity [9] and some studies do not show an independent association between OSA and IL-6 and/or CRP levels [10-12]. Other studies carried in obese patients with and without OSA, found that untreated OSA, rather than obesity, is a major determinant of vascular endothelial dysfunction, inflammation, and elevated oxidative stress in obese patients [13].

Among patients with OSA, the systemic inflammatory variability response can be explained by different pattern of epigenetic modifications induced by the apneic episodes and consequently altered expression of genes involved in the atherosclerotic process. Continuous hypoxia can induce hypermethylation of genes involved in cardiovascular diseases [14,15], but the role of intermittent hypoxia -a characteristic feature of OSA- is not so well known. However, increased methylation in the promoter region of the FOXP3 gene has been recently described in children with OSA and systemic inflammation [16]. The FOXP3 gene controls the differentiation of lymphocytes into regulatory T lymphocytes (Treg), a subset of T helper cells that inhibit atherosclerosis by modulating lipoprotein metabolism [17].

Most OSA patients attending sleep clinics have many confounding comorbidities, e.g. smoking and alcohol habits, obesity, dyslipemia, hypertension, etc.…,. These confounding variables are also associated with systemic low-grade inflammation that makes it difficult to determine the independent role of OSA in the pathogenesis of cardiovascular diseases. Furthermore, the onset of epigenetic changes in adults with OSA remains unknown. Our hypothesis is that changes in epigenetic regulation of systemic inflammation and metabolic dysfunction in OSA, are linked to accelerated cardiovascular morbidity. The Epigenetics Status and Subclinical Atherosclerosis in Obstructive Sleep Apnea (EPIOSA) study is a 5-yr longitudinal study with the overall aim to identify epigenetic markers associated to prevalent and progression of subclinical atherosclerosis in individuals with OSA, as well as biomarkers that may serve as surrogate end-points. The present article describes the purpose and design of the study.

## Methods/Design

### Study objective

The EPIOSA study has the following specific aims: 1) Use of questionnaires, sleep studies, carotid ultrasonography and cerebral magnetic resonance imaging (MRI) for the definition of OSA subpopulations and controls among individuals without comorbidities; 2) Identification and definition of the parameters that predict disease progression over 5 yrs of follow-up. For the purposes of the present study, disease progression is defined in terms of changes in sleep disordered breathing variables, symptoms, carotid artery intima-media thickness (IMT) and plaque and new microblebs in MRI; 3) Identification of useful biomarkers for disease progression by measuring known biomarkers that correlate with OSA severity, in blood and urine samples; 4) Identification of novel epigenetic factors and/or biomarkers correlating with poor outcomes in OSA and controls. This will be analyzed by cytometry analysis, DNA methylation in genes subserving inflammatory functions RNA transcriptomics; and 5) assessment of the effect of CPAP (Continuous positive airway pressure) on inflammatory and epigenetic mechanisms and disease progression.

### Study design

EPIOSA is a 5-yr non-interventional longitudinal prospective study being conducted at the Sleep Clinic of the Hospital Universitario Miguel Servet, a large teaching hospital in Zaragoza (Spain). Following a baseline visit, subjects are to be followed-up at 3, and then every year. All subjects will continue to receive their usual care by their primary physician and sleep specialist throughout the study. CPAP treatment will be started according to the Spanish National guidelines, free of cost for the patients [18].

### Subject participation

We have estimated to enroll up to 300 consecutive OSA male patients aged 20–60 yrs, with baseline apnea-hipopnea index ≥ 5 events per hour of sleep (AHI). In addition, we expect to recruit 50 control subjects (AHI < 5) aged 20–60 yrs and matched by body mass index (BMI). The inclusion and exclusion criteria for OSA patients and control subjects are shown in Table 1. All participants will be advised regarding life-style modification, exercise, diet and to avoid smoking or alcohol consumption.

**Table 1 T1:** Selection criteria

** *Inclusion criteria* **	** *Exclusion criteria* **
● Males aged 20 – 60 years	● Any history of cigarette/tobacco smoking use
● AHI ≥ 5 events per hour of sleep (OSA group) and AHI < 5 (control group)	● Alcohol abuse
● Willingness to participate in the study and complying with the study by signing a written informed consent	● Arterial blood hypertension (arterial blood pressure: ≥140 mmHg systolic and/or ≥90 mmHg diastolic or taking antihypertensive medication)
	Low high-density lipoprotein (HDL) cholesterol (<40 mg/dL) or high LDL cholesterol (≥130 mg/dL) or taking lower lipid drugs.
● Available for study visits over 5 years	● Fasting plasma glucose >126 mg/dl or taking anti diabetic medications
	● Other metabolic diseases (e.g., hypothyroidism)
	● Present or past history of vascular diseases, including myocardial infarction, angina, coronary artery procedures (coronary artery bypass graft or percutaneous coronary intervention), aneurysm, transient ischemic attack or stroke.
	● Autoimmune diseases
	● Past or present history of malignancies
	● Chronic inflammatory diseases (e.g., Crohn disease)
	● Chronic infectious diseases (e.g., chronic viral hepatitis)
	● Chronic respiratory diseases (e.g., asthma)
	● Morbid obesity (body mass index ≥40 kg/m^2^)
	● Any chronic oral therapy
	● Sleep disorders other than OSA
	● Having undergone upper airway surgery
	● Having previously use CPAP therapy

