Part of the blood samples collected in EDTA tubes are stored at -80°C until DNA isolation, which is performed in the Department of Molecular Biology at the Faculty of Veterinary of the University of Zaragoza. Genomic DNA is obtained with the use of the illustra blood genomic Prep Midi Flow Kit (GE Healthcare, UK) following the manufacturer’s instructions. Genome-wide DNA methylation profiles will be studied in approximately 1 μg of genomic DNA treated with sodium bisulfite. The converted DNA will be analyzed using Illumina’s Infinium Human Methylation 450 BeadChip assay (Illumina, San Diego, CA, USA). To minimize position effects, cases and controls will be randomly distributed. The assay allows determination of DNA methylation levels at >450,000 CpG sites covering all designable RefSeq genes, including promoter, 5′, and 3′ regions. It captures CpG islands and shores, non-CpG methylated sites, microRNA promoter regions and disease-associated regions identified through genome-wide association studies [24]. Illumina array data will be processed using the Methylation Module of GenomeStudio v1.9 software. To identify differentially methylated regions (DMRs), we will use a 1-kb sliding window and apply Fisher’s method to combine P values for each 1-kb region on the basis of all probes within each window [25]. Significant DMRs will be selected at a 1% FDR on autosomes and 5% FDR on chrX. After statistical analyses, the methylation patterns of the gene of interest will be confirmed by sequencing of the 24 bisulfite-treated DNA samples used for the genome wide analysis.

#### **
*Gene expression analysis*
**

Blood samples stored at -80°C in PaxGene (TM) tubes will be used for total RNA isolation using PAXgene Blood RNA Kit (Qiagen, Venlo, Netherlands). Quantitative real time polymerase chain reactions (qRT-PCR) will be performed to test whether differential methylation patterns of the selected genes affect their expression level. Complementary DNA will be synthesized from total RNA using random hexamers and the SuperScript^®^ III First Strand Synthesis Kit (Life Technologies, Carlsbad, California, US). Primers and TaqMan^®^ probes will be selected from the Applied Biosystems Inventories Assays and qRT-PCR will be performed in a The StepOne™ Real-Time PCR System (Applied Biosystems, Life Technologies, Carlsbad, California, US).

#### **
*MicroRNA analysis*
**

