### Statistical analyses

Groupwise comparisons (n >2) will be performed using a nonparametric Kruskal-Wallis test followed by a Mann–Whitney U test as appropriate. Pairwise comparisons were performed using a nonparametric Mann–Whitney test unless otherwise indicated. Chi square tests will be performed for categorical variables. Regression models will be applied to assess the effect of OSA, biomarkers, peripheral lymphocytes and epigenetic changes on CIMT, carotid plaque and cerebral microbleeds. All models will be adjusted for age and BMI, and additionally for covariables that may change the estimated risk beyond 5% Specific statistics procedures will be performed for the arrays as described above. STATA-12 for Windows (STATA CORP, TX, USA) are to be used for all analyses.

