There are many potential mechanisms linking OSA, endothelial dysfunction, atherosclerosis and cardiovascular diseases. Sleep loss and fragmentation could trigger endothelial dysfunction and immune response but its remains to be demonstrated if this occurs in patients with OSA. Chronic intermittent hypoxia (CHI) is the other hallmark of OSA. CIH can induce endothelial dysfunction independently of respiratory effort in animal models [37]. In patient with OSA, oxygen desaturation index (ODI), a surrogate of CHI severity has been associated with endothelial dysfunction [38]. On the other hand, ODI emerged as an independent predictor of carotid and aortic wall thickness in OSA patients using cardiovascular magnetic resonance study [39]. CPAP treatment of OSA significantly reduces carotid intima-media thickness, supporting the concept that OSA is an independent risk factor for atherosclerosis [31]. There is growing evidence that OSA is associated with increased activation of immune and inflammatory cells including circulating monocytes, platelets and lymphocytes and proinflammatory cytokines such as leukotrienes, interferon-γ, TNF-α and IL-6 have been reported elevated in OSA [8]. CRP levels have been particularly studied with conflicting results [7,40]. The intermediate process for an increased risk of atherosclerosis in OSA could be the presence of this systemic inflammation and immunity activation as a result of the CHI. There is no evidence of genetic alterations in patients with OSA that favor the development of systemic inflammation, changes the adaptive immunity or that specifically encourage the emergence of early atherosclerosis. However, it is likely a different response from the pro-inflammatory genes to CIH. This response depends in part on epigenetic mechanisms that promote or suppress the expression of these genes. Recently in pediatric OSA those children with elevated CRP, were more likely to have increased DNA methylation of the FOXP3 gene [16]. This result in a reduced Treg population and in a swift Th1:Th2 balance towards Th1 predominance [29]. These immune-inflammatory changes favor endothelial dysfunction and a pro-atherogenic state and ultimately an increased risk for cardiovascular diseases. If those mechanisms also play a role in accelerated atherosclerosis in adults with sleep apnea is unknown. In conclusion, the current study is novel in several ways: 1) It is the first study to evaluate the relationship between baseline OSA phenotypes and normal matched controls without comorbidities and subclinical atherosclerosis and 2) it will allow prospective analysis of inflammatory biomarkers, as well as methylation and miRNA abnormalities in non-OSA subjects and patients with treated or non-treated OSA. Our results may provide more information on the association of OSA and cardiovascular diseases and possibly identifying novel targets for therapeutic intervention. It could also provide evidence that CPAP can not only improve daytime symptoms, but also have a positive effect on progression of subclinical atherosclerosis.

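### Controls are matched on BMI but not age, and the stated OSA-versus-control comparisons of T cells and methylation carry no age adjustment, so an age gap may pass for an OSA effect

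*Protocol article*

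**What the plan says.** Under Subject participation, the OSA group is described as follows: "We have estimated to enroll up to 300 consecutive OSA male patients aged 20–60 yrs". For the comparison group, "we expect to recruit 50 control subjects (AHI < 5) aged 20–60 yrs and matched by body mass index (BMI". Table 1 gives both groups the same age limits. BMI is the only matching factor named anywhere in the article.

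Under Statistical analyses, three rules bear on the point:

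- Group comparisons: "Groupwise comparisons (n >2) will be performed using a nonparametric Kruskal-Wallis test followed by a Mann–Whitney U test as appropriate", and "Pairwise comparisons were performed using a nonparametric Mann–Whitney test unless otherwise indicated".
- Regression: "Regression models will be applied to assess the effect of OSA, biomarkers, peripheral lymphocytes and epigenetic changes on CIMT, carotid plaque and cerebral microbleeds". The next sentence puts age and BMI into every one of these models.
- Arrays: "Specific statistics procedures will be performed for the arrays as described above".

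The array procedure, under DNA methylation analysis, combines probe P values within 1-kb windows by Fisher's method and selects regions by false discovery rate. Its one stated balancing step is "To minimize position effects, cases and controls will be randomly distributed". The section puts the number of samples in the genome-wide analysis at 24 and gives neither the case/control split nor the way they are chosen.

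**The concern.** By putting age into every regression model, the plan itself treats age as a confounder. Yet T-cell subsets and methylation appear in those models only as predictors of the vascular outcomes. No stated model has them as the outcome with OSA status as the exposure and age as a covariate.

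Such direct contrasts are nonetheless intended. Power considerations justifies the sample size partly by earlier paediatric findings of a reduced Treg population and of altered methylation in OSA against non-OSA controls. The second novelty claimed in the Discussion is the analysis of biomarkers, methylation and miRNA in non-OSA subjects and in treated or untreated OSA patients.

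For these contrasts, age is controlled neither by the stated design nor by the stated analysis. If the controls are on average younger or older than the patients, an age-related marker will differ between the groups with no OSA effect behind it.

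**Working it through.** **Step 1. The plan's own group sizes.** Power considerations expects 2% loss per year over 5 years and 270 OSA and 45 non-OSA men at the end. 300 × (1 − 5 × 0.02) = 270 and 50 × (1 − 5 × 0.02) = 45. Compounding gives 300 × 0.98⁵ = 271.2 and 50 × 0.98⁵ = 45.2. The figures reproduce.

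**Step 2. Where age is controlled.**

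- Recruitment: BMI matched; age limited to 20–60 years in both groups but not matched.
- CIMT, plaque and microbleeds by OSA status: regression adjusted for age and BMI.
- T-cell subsets by OSA status: Kruskal-Wallis and Mann-Whitney tests, which take no covariates.
- Methylation by OSA status: separate array procedure; random placement deals with position on the array, not with age; no covariate stated.

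**Step 3. Size of the effect.** The documents give neither the age distribution nor any age-outcome correlation, so the following are assumptions: age SD 10 years within each group, a mean age gap Δ, a within-group correlation r between age and the marker of 0.2 to 0.6, a linear age effect, and no true OSA effect. With the marker scaled to SD 1:

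- shift caused by age: δ = r × Δ / 10
- standard error: √(1/45 + 1/270) = 0.161
- two-sided false-positive rate at 0.05: Φ(δ/SE − 1.96) + Φ(−δ/SE − 1.96)

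For Δ = 5 years:

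- r = 0.2: δ = 0.10, δ/SE = 0.62, rate 0.095
- r = 0.4: δ = 0.20, δ/SE = 1.24, rate 0.237
- r = 0.6: δ = 0.30, δ/SE = 1.86, rate 0.462

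Over the same range of r, a gap of 0 years gives 0.05, 2 years gives 0.06 to 0.12, and 8 years gives 0.17 to 0.85. With the baseline numbers of 50 versus 300, a 5-year gap gives 0.10, 0.26 and 0.50.

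**Step 4. Check by simulation** (4,000 runs per setting, 45 versus 270). With a 5-year gap, the Mann-Whitney test rejects in 0.10, 0.22 and 0.45 of runs at r = 0.2, 0.4 and 0.6. Least squares with age as a covariate rejects in 0.053, 0.049 and 0.053. With no age gap (r = 0.4), the rates are 0.050 for Mann-Whitney and 0.047 for the adjusted model.

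**Step 5. The array subset.** Assuming that the 24 samples are 12 versus 12, the standard error is √(2/12) = 0.408. A 5-year gap then gives 0.057, 0.078 and 0.114 per test at 0.05. The inflation per test is smaller because the groups are small. These are single-test rates and do not carry over directly to window-combined P values selected by false discovery rate.

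**The case against.** The strongest reply is that the main outcome is already protected. A reader might infer that the OSA effect on CIMT is confounded by age too, particularly as the Discussion presents as the first novelty the "relationship between baseline OSA phenotypes and normal matched controls without comorbidities and subclinical atherosclerosis". The documents do not support that: the effect of OSA on CIMT, plaque and microbleeds is assessed in models that all include age and BMI. Only an additional unadjusted rank comparison of CIMT would be exposed.

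Nor does aim 4 rest on an OSA-versus-control contrast. It concerns markers that correlate with poor outcomes, and the regressions address such associations with age adjustment.

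A reader might also infer that 24 array samples are biased simply because age could be unbalanced by chance. That is not bias. Without a systematic age difference an unadjusted test keeps its nominal error rate, because the variation in age is part of the variation in the outcome.

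A systematic gap is itself undocumented. That men with AHI below 5 are younger at equal BMI is plausible, but the article does not say so, and both groups share the same limits.

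Finally, this is a condensed article. Array covariates and sample selection may be set out in a fuller protocol or analysis plan, so silence there is not an error in itself.

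All of this stands, and it narrows the point. What remains is what the article does state: BMI as the matching factor, which no later analysis plan can alter once controls are recruited, and covariate-free rank tests for group comparisons. Matching on one confounder and modelling another is legitimate, but here the modelling is stated only for the vascular outcomes.

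**Conclusion.** The point holds as a conditional one, limited to direct OSA-versus-control comparisons of T-cell subsets and DNA methylation. If the groups differ in age, part of any such difference may be due to age. Under the assumptions of Step 3 with a 5-year gap, the unadjusted false-positive rate for a T-cell marker at nominal 0.05 is about 0.10 to 0.45; with no gap it stays at 0.05. For single array tests under an assumed 12 versus 12 split, it is about 0.06 to 0.11. The size rests wholly on the assumed gap, age SD and correlations. The direction of any gap is unknown, but the rates are two-sided and do not depend on it. The vascular regressions and the chosen age range are not faulted. This is an inexpensive improvement to make while controls can still be chosen, not a defect that undermines the study.

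**What to change.** - **Subject participation:** frequency-match the 50 controls to the OSA group on age bands (10-year bands, for example) as well as BMI.
- **DNA methylation analysis:** choose the array samples so that OSA and control men are balanced on age, state the split, and include age in the probe-level model before P values are combined within windows.
- **Statistical analyses:** name an age- and BMI-adjusted regression, rather than the Mann-Whitney test, as the reported OSA-versus-control comparison for T-cell subsets and methylation. The rank tests can remain as descriptive results.

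Age and BMI are already available for every participant, so no new measurement is needed. The costs are one more matching variable for 50 men, one more covariate in the models, and possibly slightly slower control recruitment in some age bands. If recruitment is too far advanced to match, the adjusted analysis is still worth adopting, but it cannot make up for age ranges that scarcely overlap.
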